### Eligibility criteria

Patients will be identified and selected by their clinicians based on their TCSS. The inclusion criteria are as follows: men or women aged 18–75 years; a diagnosis of DPN (no limitation on the degree of DPN) [22]; agreement to comply with the clinician’s treatment plan; TCSS scores of ≥ 6 points [23, 24]; and ability to understand and complete the informed consent process and consent to participate in the study.

The exclusion criteria are as follows: other neuropathies such as cervical or lumbar lesions (nerve root compression, spinal stenosis, cervical and lumbar degeneration), cerebral infarction, Guillain-Barre syndrome, or severe arteriovenous vascular lesions (venous thrombosis, lymph tube inflammation); lower extremity skin ulcers or gangrene, lower extremity edema, or suffering from skin diseases; diabetic ketoacidosis, hyperglycemia hypertonic syndrome, diabetes lactic acidosis, and other acute complications; patients with malignant tumors or severe dysfunction of the heart, liver, and kidneys; pregnancy or breast-feeding; participation in other similar interventions; mental disorders that render the patient unable to understand the nature of the study, its scope, and possible outcomes or unable to follow the doctor’s advice.

### Intervention

#### TW decoction and control drug

TW decoction is a Chinese medicinal formula prescribed for DPN treatment. It is composed of cayenne/chili pepper (*Capsicum annuum* Linn.), red Sichuan peppercorns (*Zanthoxylum bungeanum* Maxim.), frankincense (*Boswellia carterii*), myrrh (*Commiphora myrrha*), honeysuckle vine (*Caulis lonicerae*), borneol (derived from the camphor tree, *Cinnamomum camphora*), and safflower (*Carthamus tinctorius*). The control drug will be made of one-tenth of the dry weight of the TW decoction extracts and is similar to the TW decoction in appearance, shape, weight, smell, and color. The herbs for both groups will be extracted and made into granules that are soluble in hot water. Jiangyin Tianjiang Pharmaceutical Company (Wuxi, China) will produce the granules used in this study. TW decoction or control drug is shown in Fig. 2.

**Fig. 2 Fig2:**
[figure not shown]
TW decoction or control drug

The drug will be prepared as follows. The herbs *Capsicum annuum* Linn., *Zanthoxylum bungeanum* Maxim., *Boswellia carterii*, *Commiphora myrrha*, *Caulis lonicerae*, and *Carthamus tinctorius* will be boiled with water separately twice: for 1.5 h the first time and 1 h the second time. The liquid will be filtered, condensed into a paste, and then spray-dried and formed into granules. Borneol will be comminuted into a fine powder. The seven herbal granules will be packed together according to the dose of the TW decoction. As there are seven types of herbal granules that will be packed separately before being combined into one dose, the control drug must be produced separately as well; each herb will have its individual control drug. For the control drug, one-tenth will be composed of the herbal extract and the remaining portion will be composed of lactose, caramel pigment, sunset yellow, lemon yellow, picric acid, etc. to maintain a similar appearance, shape, weight, smell, and color to the corresponding herb.

Patients will be provided with education regarding foot care, diet, and physical activity by an investigator; dose modifications of current antidiabetic, lipid, and blood pressure medications will be allowed at the discretion of the investigator.

### Exclusion of patients receiving certain therapeutic drugs and concomitant treatments

This trial will exclude patients receiving the following therapeutic interventions: neuroprotective drugs; other TCM formulas; and other concomitant treatments. The above events will be discussed with the physician in charge and carefully recorded.

### Outcome measures

All of the baseline, in-treatment, and follow-up evaluations will be performed by experienced investigators. All outcome measures are shown in Fig. 3.

**Fig. 3 Fig3:**
[figure not shown]
Scheduled events

### Primary outcome measures

#### Toronto Clinical Scoring System

The TCSS is a scale used to diagnose and evaluate DPN. This scale was proposed by diabetic and neuropathy scholars in Toronto, Canada, in 2001 and they later assessed its validity and reliability [24–26]. In China, researchers also revealed that TCSS has good validity [27].TCSS is composed of three parts: six symptom scores (the presence or absence of foot pain, numbness, tingling, weakness, imbalance, and upper limb symptoms); eight reflex scores (bilateral knee and ankle reflexes); and five physical examination scores (the presence or absence of pinprick, temperature, light touch, vibration, and position sense). Score grading will be stratified as ≤ 5 indicating no neuropathy, 6–8 indicating mild neuropathy, 9–11 indicating moderate neuropathy, and 12–19 indicating severe neuropathy.

### Secondary outcome measures

#### Nerve conduction velocity

All patients will be examined by electromyography at baseline, at the end of the treatment, and at completion of follow-up. The bilateral motor and sensory nerve conduction velocity of the median and common peroneal nerve will be calculated.

#### Blood glucose

Glycemic indices including fasting blood glucose (FBG), postprandial blood glucose (PBG), and glycosylated hemoglobin (HbA1c) will be measured at baseline, at the end of the treatment period, and at completion of follow-up. All blood samples will be taken in the morning: 2 mL fasting venous blood will be collected for measurement of FBG and another 2 mL for HbA1c. For measurement of PBG, 2 mL venous blood will be taken 2 h after breakfast.

#### Blood lipids

Blood lipids indices including total cholesterol (TC), total glycerides (TG), high-density lipoprotein (HDL), and low-density lipoprotein (LDL) will be measured at baseline, at the end of treatment, and at completion of follow-up. Here, 2 mL fasting venous blood will be taken for measurement of blood lipids in the morning.

#### Serum inflammatory cytokines

Serum inflammatory cytokines, including tumor necrosis factor-α (TNF-α), interleukin-6 (IL-6), and C-reactive protein (CRP), will be measured at baseline, at the end of treatment, and at the completion of follow-up. Fasting venous blood will be taken in the morning to measure TNF-α, IL-6, and CRP, each requiring 2 mL blood.

#### European Quality of Life Five-Dimension Scale

EQ5D is a self-administered, easy-to-use questionnaire. It comprises two parts: a self-reported description and a self-rated health status. The self-reported description uses a five-dimensional classification consisting of mobility, self-care, performance level of routine activities, pain/discomfort, and anxiety/depression. Each dimension is graded according to the difficulty in performing the tasks using the following statements: “no problem,” “some problem,” or “extreme problem”. The self-rated health status uses a visual analog scale or “thermometer” (perfect health = 100; worst health = 0) [21, 28]. The validity and reliability of EQ5D have been evaluated by different researchers [20, 29]. The researchers will explain what each dimension means and how to complete the questionnaire before giving it to the participants. Patients are required to complete the questionnaire by themselves after coming to fully understand it. Researchers will collect the questionnaires immediately after patients complete them.

#### TCM symptom score

TCM symptom scores are assessed using a specialized scoring system that is derived from the guiding principles of clinical research on new TCM drugs [19]. The TCM symptom scoring sheet includes four items: limb numbness; limb pain; limb chills; and limb weakness. Each item is divided into four levels and a total of 12 points are calculated (no = 0 points, mild = 1 point, moderate = 2 points, severe = 3 points). Researchers will complete TCM symptom score sheets by interview.

### Patient timelines for study participation

The schedule for enrollment, intervention, assessment, and follow-up are listed in Fig. 3.

### Sample size

The primary outcome measure of the study is TCSS; hence, the sample size will be calculated based on preliminary TCSS results. We anticipate that TCSS scores will decrease 3.5 points in the TW foot bath group compared with 1.5 points in the control group [30, 31]. Based on a two-tailed type-1 error of 0.05 and a type-2 error of 0.099, we anticipate that 266 patients will need to be recruited for each group. Given the possibility of exclusion or lost follow-ups, an increase of 20% will be required for the sample size; therefore, 320 patients will be enrolled in each group.

### Recruitment and consent

Patients that qualify for the study will be identified by their personal physicians and referred to the local research team. The research team consists of clinicians who are familiar with DPN diagnosis and treatment. In addition, the research team will receive appropriate training regarding all the relevant information pertaining to the study. Patients will be screened based on the inclusion and exclusion criteria. If eligible, patients will be informed of the study details and will discuss their health condition and treatment procedures with their case researcher. Researchers at each clinical site will be trained to follow the consent procedures for this study. All patients will be offered a minimum of 24 h to consider enrollment before providing written informed consent. Informed consent will be obtained before the start of the trial.

### Randomization

A block randomization sequence will be generated by SAS 9.2 software (SAS Institute Inc., Cary, NC, USA) with block size set at four, to be performed by an independent staff of the Key Unit of Methodology in Clinical Research (KUMCR) of Guangdong Provincial Hospital of Chinese Medicine. Eligible participants will be randomly allocated to either the experimental group or the control group at a ratio of 1:1 through the Central Randomization Management System developed by KUMCR. At each clinical site, randomization will be also performed at a 1:1 ratio to ensure even distribution.

### Allocation concealment

The randomization list and blinding codes will be kept strictly confidential and only the KUMCR staff will have access to them. Allocation concealment will be ensured until the entire program is complete.

### Blinding

The patients will be blinded to the treatment that they are provided. The investigator and clinical pharmacist will be also blinded to the randomization. Only the KUMCR staff will have access to the randomized treatment allocation table. All investigators, participants, and related medical staff will remain unaware of intervention assignments throughout the trial. The research team will agree to view the blinding allocation only after completion of the trial. In the event of a medical emergency where the patient’s past treatment history is necessary for immediate medical management or treatment decisions, the investigator will un-blind the study. The investigator will attempt to contact the project leader first and then contact the relevant statistician to use a separately arranged emergency code to unlock the blinded treatment code.

### Data collection and management

Data collection will be performed before, during, and after treatment, as well as during the routine follow-up period (Fig. 3). The data will be recorded on the predesigned case report forms (CRF) and entered into an electronic data capture system. All private and sensitive data will be removed. All identification information regarding the patients will be coded.

### Statistical analysis

A statistician blinded to the patient allocation for each group will perform all analyses using PASW Statistics 17.0 software. Statistical analysis will be performed on an intention-to-treat (ITT) basis with 95% CI. The ITT analysis will include all randomized patients. All data will be presented as mean ± standard deviation and compared between groups using unpaired Student’s *t*-tests. Comparisons within a group will be performed using analysis of covariance. Count data will be analyzed using chi-square tests. Repeated measure ANOVA will be performed to assess the changes within and between groups over time. Subgroup analyses will be performed according to the treatment periods. *P* < 0.05 will be considered statistically significant.

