**Methods/design:**

This study is a multicenter, double-blind, randomized controlled trial. A total of 640 DPN patients will be recruited and randomized to receive a foot bath with either the TW decoction or control drug. Participants will be assessed at baseline and 12 and 24 weeks after treatment. The primary outcome was the change of the Toronto Clinical Scoring System (TCSS). Secondary outcomes were nerve conduction velocity, blood glucose, blood lipids, serum inflammatory cytokines, and the European Quality of Life Five-Dimension Scale (EQ-5D) and TCM symptom scores.

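### Analysis of covariance is assigned to within-group comparisons, while the between-group TCSS comparison gets tests with no stated baseline or site adjustment and no named primary, at a cost in precision

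*Protocol article*

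**What the plan says.** The Statistical analysis section of the protocol article names three methods for continuous outcomes:

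- **Between groups:** "All data will be presented as mean ± standard deviation and compared between groups using unpaired" Student's t-tests. No covariate is mentioned.
- **Within groups:** "Comparisons within a group will be performed using analysis of covariance". No covariate is mentioned here either.
- **Over time:** "Repeated measure ANOVA will be performed to assess the changes within and between groups over time". No baseline or site term is stated.

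The section does not say which of the two between-group methods is primary.

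Three other parts of the article bear on this. The Abstract defines the primary outcome as the change in TCSS. Eligibility criteria requires "TCSS scores of ≥ 6 points" with no limit on severity, so on the scale described under Primary outcome measures the baseline can run from 6 to 19. The Randomization section sets blocks ("with block size set at four") and adds: "At each clinical site, randomization will be also performed at a 1:1 ratio to ensure even distribution".

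**The concern.** Within a single arm there is no treatment contrast for ANCOVA to adjust, so the instruction cannot be carried out as a meaningful ANCOVA and the analyst would have to improvise. The comparison that answers the trial's question could use the method, but is assigned a test without it.

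Two pieces of information are therefore left unused. Baseline TCSS is recorded for everyone and probably predicts the outcome. Site is balanced by the allocation. I read the site-level 1:1 statement as blocks within site, although the article does not use the word stratified. When allocation is balanced within sites and the sites differ, an analysis without site overstates the standard error.

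At stake are the width of the primary confidence interval, protection against chance baseline imbalance, and clarity about which test decides the trial.

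**Working it through.** **Inputs from the article.** The difference is 3.5 − 1.5 = 2.0 points, two-sided alpha is 0.05, type-2 error is 0.099 (power 0.901), and there are 266 per group before the dropout allowance (Sample size). Eight sites are listed (Table 1).

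**Inputs not in the article, so assumed.** Baseline/follow-up correlation r = 0.3 to 0.7; site share of variance (ICC) 0 to 0.10.

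**The plan's own figure.** No SD is given, so 266 can only be solved backwards: SD = 2.0 / [(1.960 + 1.287) × √(2/266)] = 2.0 / 0.2816 ≈ 7.10. Putting SD 7.10 back in returns 266 per group and power 0.901. I use this SD below only to put the loss in TCSS points; whether it is plausible is a separate matter.

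**Step 1: baseline adjustment, equal baseline and follow-up variances.** With common SD σ, the variance of a change score is 2σ²(1 − r) and the ANCOVA residual variance is σ²(1 − r²). The ratio is (1 − r²) / [2(1 − r)] = (1 + r)/2, so the CI-width ratio is √((1 + r)/2).

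| r | CI-width ratio, ANCOVA / t-test on change | Narrower by |
|---|---|---|
| 0.3 | √0.65 = 0.81 | 19% |
| 0.5 | √0.75 = 0.87 | 13% |
| 0.7 | √0.85 = 0.92 | 8% |

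If the t-test were run on the final score instead, the ratio would be √(1 − r²) = 0.95, 0.87 and 0.71.

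**Step 2: the same in TCSS points.** If 7.10 is the SD of change, the t-test half-width is 1.96 × 7.10 × √(2/266) = 1.21 points. ANCOVA gives 0.97, 1.05 and 1.11 for r = 0.3, 0.5 and 0.7. Power rises from 0.901 to 0.981, 0.963 and 0.941. The original power would need 266 × (1 + r)/2 = 173, 200 and 227 per group.

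**Step 3: unequal variances.** Entry at TCSS 6 or more truncates the baseline and may shrink its SD relative to follow-up. With k = baseline SD / follow-up SD, the variance ratio becomes (1 − r²) / (1 + k² − 2rk). At r = 0.5 and an illustrative k = 0.7 it is 0.75 / (1 + 0.49 − 0.70) = 0.75 / 0.79 = 0.95, so the CI is only about 2.6% narrower. At k = r the ratio is 1 and the gain is nil. It is never negative, apart from the trivial cost of estimating a slope.

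**Step 4: site.** With allocation balanced within site, removing site variance multiplies the CI width by √(1 − ICC), where ICC is the site share of variance of the quantity analysed. This is 1.00, 0.975 and 0.949 for ICC 0, 0.05 and 0.10, a narrowing of 0 to about 5%. Leaving site out gives a true two-sided error of 2[1 − Φ(1.96/√(1 − ICC))] = 0.044 at ICC 0.05 and 0.039 at 0.10, against a nominal 0.05.

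**Simulation check** (4,000 trials per setting, 8 sites, blocks of four within site, 532 patients). Without site effects, the ANCOVA/change ratios were 0.806, 0.867 and 0.923, matching Step 1. With a site effect of ICC 0.10 shared by baseline and follow-up, the unadjusted t-test on the final score rejected in 3.8 to 4.1% of null trials and the adjusted analysis in 4.7 to 5.3%. In that setting the t-test on change lost nothing further, because a shared site shift cancels by subtraction.

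**The case against.** The strongest reply is that nothing here threatens validity. Under randomisation the unpaired t-test is unbiased and does not inflate type I error. A t-test on change also uses baseline by subtraction. A reader might infer that the plan ignores baseline, or that its efficacy result would be wrong; the article supports neither. It also includes a repeated-measures ANOVA, so the t-test is not the only between-group method. All of this stands. The repeated-measures ANOVA does not remove the defect, because it too states no baseline or site term and is not ranked against the t-test.

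A second reply is that covariates are commonly left to an analysis plan, which is not shown. That would answer an omission. Here the text positively assigns ANCOVA to the wrong comparison and an unadjusted test to the right one, so a later plan would have to contradict it.

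A third concerns size. Larger gains can be produced: with a TCSS SD of 3, r = 0.5 and a site SD of 1 or 1.5 points in mean change, the interval narrows by about 17% or 21%, and the t-test's error rate falls to about 3% in the second case. But a site SD of 1.5 equals the whole fall expected in controls ("We anticipate that TCSS scores will decrease 3.5 points in the TW foot bath group compared with 1.5 points in the control group") and is 2.25/(9 + 2.25) = 20% of the variance. The documents give no site variance to support it. Conversely, with an SD of change near 3 the planned difference is 2.0/(3 × √(2/266)) ≈ 7.7 standard errors, so a 13% narrower interval would not alter the conclusion.

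Two further inferences are tempting. The entry threshold makes some fall through regression to the mean likely in both arms, so within-group P values might be presented as efficacy; but the article frames its hypothesis and objectives as comparisons with control, and nothing says they will be so used. Skewness of the inflammatory markers and triglycerides under raw-scale t-tests is at most secondary, since the article gives no distributional data.

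**Conclusion.** The point holds as a misassignment of methods that costs precision. The within-group sentence is wrong as written, the between-group comparison has no stated baseline or site adjustment, and no primary test is named. The consequence is a wider interval than the collected data allow and, if sites differ in the quantity analysed, a slightly conservative test. It is not bias or excess false positives.

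The size rests on assumptions, because the article gives no SD, correlation or site variance. With r from 0.3 to 0.7 and equal variances, the loss against ANCOVA is about 8 to 19% of the width of a t-test interval on change. It shrinks, possibly to almost nothing, if truncation at entry makes the baseline SD clearly smaller than the follow-up SD. Site adjustment alone is worth about 0 to 5% for an ICC of 0 to 0.10. This should be fixed, but it would not invalidate the trial if left. That the two methods were accidentally swapped is a plausible guess about origin; the text shows only where they ended up.

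**What to change.** Rewrite the relevant sentences of the Statistical analysis section so that:

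1. The primary between-group analysis of TCSS change is an ANCOVA, or an equivalent mixed model, with treatment, baseline TCSS and site, reported as an adjusted difference with 95% CI.
2. This analysis is named as primary, and the unpaired t-test and the repeated-measures ANOVA are labelled supportive.
3. Within-group changes are reported descriptively or by paired test, not by ANCOVA.

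The cost is wording only. Baseline TCSS and site are already recorded, and the plan already relies on its software for ANCOVA. The change should be made and dated before unblinding, since afterwards it would look like a choice of primary analysis made with the results in view.

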## Methods/design

### Study design

The protocol was designed according to Standard Protocol Items: Recommendations for Interventional Trials (SPIRIT) 2013. For the SPIRIT 2013 Checklist, see Additional file 1. This trial was registered at the Chinese Clinical Trial Registry (ChiCTR-IOR-16009331) and any significant protocol changes were revised accordingly. The prospective trial was designed following the principles of multicenter, double-blinded, and was controlled at a randomization of 1:1. The aim was to evaluate the therapeutic efficacy and safety of TW foot baths for DPN treatment. Patients who agree to participate in the study will be asked to provide written informed consent. Patients will be randomly allocated to either the TW experimental group or the control group after attending an educational session related to the clinical study. Patients will receive a foot bath for half an hour once a day (daytime and night are both acceptable) for two weeks and then stop for two weeks; this cycle constitutes a therapeutic course. All patients will be required to visit their clinicians every two weeks to be evaluated. If their Toronto Clinical Scoring System (TCSS) scores are < 6 points, the foot baths will be terminated and the patients will be followed up. If the TCSS scores are > 6 points, patients will receive a total of three therapeutic courses and then be followed up. All patients will be followed for three months after treatment. During the follow-up period, patients will be required to stop the foot baths and visit their clinicians monthly. Patients who drop out due to side effects or personal reasons will be also followed up. The flow chart of the trial is outlined in Fig. 1.

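### Repeated-measures ANOVA, the only longitudinal method named, drops patients with an incomplete TCSS series and so does not fit an ITT analysis of all randomised patients unless missing values are imputed

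*Protocol article*

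**What the plan says.** All the analysis text is one paragraph of the protocol article, Statistical analysis.

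- Analysis set: "The ITT analysis will include all randomized patients".
- Between-group comparison: data are to be "compared between groups using unpaired Student’s" t-tests.
- Course over time: "Repeated measure ANOVA will be performed to assess the changes within and between groups over time". No other method in the paragraph handles more than one time point jointly.
- Software: the statistician "will perform all analyses using PASW Statistics 17.0 software".

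The paragraph does not say which method is the primary test of TCSS, whether baseline is a level of the time factor, or which ANOVA term is to be read.

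Three other places bear on the point. The abstract sets the assessment times: "Participants will be assessed at baseline and 12 and 24 weeks after treatment". Sample size raises 266 per group by 20% to 320, with the reason "Given the possibility of exclusion or lost follow-ups". Adverse events has patients with a serious adverse event leave the study, while Study design says that patients who drop out for side effects or personal reasons are still followed up.

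**The concern.** Classical repeated-measures ANOVA needs a complete row for each patient: one missing time level removes the patient and all of that patient's other values. A plan that expects incomplete records and also counts every randomised patient has therefore named a method that cannot deliver its own analysis set by itself.

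Two things are at stake. First, a patient seen at week 12 but lost before week 24 would contribute nothing, not even to the end-of-treatment comparison, although the value was measured. If loss depends on how the patient was doing at week 12, the remaining completers are a selected group and the comparison is no longer that of the randomised groups. Second, if baseline is a level of the time factor, the group main effect averages a baseline difference that is zero by randomisation with the post-treatment differences. It then does not estimate the treatment effect for which the trial was sized.

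**Working it through.** **1. How many patients the method could leave out**

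Inputs from Sample size: 266 per group needed, a 20% increase, 320 per group enrolled.

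- The plan's own step: 266 × 1.20 = 319.2, rounded to 320. This reproduces.
- Read as the number the plan can lose and still keep 266: 320 − 266 = 54 per arm (16.9%), 108 of 640 in total, leaving 532.
- Read as a loss of 20% of those enrolled: 320 × 0.20 = 64 per arm, 128 of 640 in total, leaving 256 per arm or 512.

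These are upper figures for the conflict. The allowance covers exclusion as well as loss, and not every lost patient will have a week-12 value to discard.

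**2. What listwise deletion could do to the week-12 difference (illustration)**

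The documents give no loss pattern and no SD, so both are assumed here. Anticipated mean improvements are 3.5 (TW) and 1.5 (control). Suppose all patients are seen at week 12, then 40% of those who improved by less than 1 point and 8% of the others miss week 24. With improvement normal with mean m and SD s, let a = (1 − m)/s, P = Φ(a) and E = mP − sφ(a). Then loss = 0.08 + 0.32P, and the completers' mean = (0.92m − 0.32E)/(1 − loss).

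| SD of change | Loss, TW v control | Completers' week-12 mean, TW v control | Difference (true 2.0) |
|---|---|---|---|
| 3 | 14.5% v 21.9% | 3.82 v 1.98 | 1.83 |
| 7.1 | 19.6% v 23.1% | 4.56 v 2.68 | 1.88 |

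The shift is 0.12 to 0.17 points, against TW. In this scenario loss depends only on the observed week-12 value, so a likelihood model that uses every week-12 value is aimed at the full 2.0.

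**3. The conditional dilution**

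With k time levels including baseline, equal groups at baseline and the same effect δ at each later level, the group main effect is δ(k − 1)/k.

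- Baseline, week 12 and week 24: (0 + 2 + 2)/3 = 1.33.
- Baseline and one later time: (0 + 2)/2 = 1.0.
- Group-by-time contrast, later mean minus baseline: (2 + 2)/2 − 0 = 2.0, undiluted.

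Power has to rest on an assumed SD. The one that 266 per group implies is 2 × √(266/2) / (1.960 + 1.287) = 7.10 for the change. Assume compound symmetry with correlation ρ, visit SD s = SD of change / √(2(1 − ρ)), SD of a patient's mean over three levels = s√((1 + 2ρ)/3), and 256 complete cases per arm:

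| SD of change | ρ | Visit SD | Power, group main effect (1.33) | Power, group-by-time contrast (2.0) |
|---|---|---|---|---|
| 7.10 | 0.3 | 6.00 | 93% | 95.7% |
| 7.10 | 0.5 | 7.10 | 74% | 95.7% |
| 7.10 | 0.7 | 9.17 | 45% | 95.7% |
| 4 | 0.5 | 4.00 | 99.6% | over 99.9% |
| 4 | 0.7 | 5.16 | 90% | over 99.9% |

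The rows with visit SD 7.10 and 9.17 should not be leaned on. Eligible baseline scores run from 6 to 19, so a baseline SD cannot exceed (19 − 6)/2 = 6.5. The firm result is the shrunken estimate, not a particular loss of power.

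**The case against.** **The analysis plan is not shown and may impute.** This stands as a condition. With imputation the ANOVA can run on all randomised patients, and the absence of an imputation rule from an article is no fault. What remains is that the method named does not by itself fit the set named.

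**The ANOVA is not called primary.** True. Unpaired t-tests are listed first, need no complete series and, applied to the change score, are not diluted. A reader might infer that the whole trial becomes a completers' analysis; the text does not support that. The ANOVA is, however, the only listed method that joins the time points, and the primary objective covers TCSS at both end of treatment and follow-up.

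**Dilution is not in the text.** A reader might infer that the planned test averages in baseline. The article speaks of changes over time, which fits the group-by-time term, and that term keeps the full 2 points. The dilution can be raised only as a reading left open.

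**Patients who stop treatment are not automatically missing.** Study design keeps drop-outs in follow-up, and Adverse events lets those with mild side effects resume. It would go too far to say that patients with skin reactions vanish from the data. Withdrawal after a serious adverse event and true loss to follow-up remain.

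**Only modelled levels count.** The article also states "All patients will be required to visit their clinicians every two weeks to be evaluated", but nothing says that these visits enter the ANOVA. Nor does the text show that patients who stop early lack the needed levels: other sections define measurement by phase (end of treatment, completion of follow-up), which early stoppers also reach.

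**A mixed model does not include everyone either.** Correct: a model of change uses no outcome from a patient without any post-baseline TCSS. It narrows the gap, and the sensitivity analysis has to cover the rest.

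**Conclusion.** The point holds in a limited form. The stated longitudinal method uses complete cases, the stated analysis set is all randomised patients, and the plan itself allows for 54 to 64 of 320 patients per arm being excluded or lost. The two do not fit unless missing values are imputed. The number actually affected depends on how many patients have some but not all of the modelled TCSS values, which the documents do not say.

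The likely bias is modest: under one assumed loss pattern the week-12 difference moves by less than 0.2 points, and other patterns could give more or less. The fall from 2.0 to 1.33 arises only if baseline is a time level and the group main effect is read. The documents settle neither, so it is a reason to specify the contrast, not evidence of a planned error. The mismatch is worth correcting because the remedy is cheap and uses data that will be collected anyway.

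**What to change.** In Statistical analysis, replace repeated-measures ANOVA for TCSS with a linear mixed model for repeated measures:

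- Outcome: TCSS change from baseline at end of treatment and at end of follow-up. State how these two labels relate to weeks 12 and 24 for patients who stop the baths early.
- Terms: treatment, visit, treatment-by-visit, baseline TCSS and site, with unstructured covariance between the two visits.
- Data: all observed post-baseline values, analysed by randomised group. Baseline is a covariate, not a time level.
- Contrast: the treatment difference at end of treatment, not an overall group main effect.
- Sensitivity: one pre-stated analysis for missing values that includes patients with no post-baseline TCSS and assumes less favourable values where TW data are missing.

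The mixed-model procedure of the named software can fit this. If the sponsor prefers to keep the ANOVA, naming the imputation method and reading the group-by-time term would also remove the conflict. The cost is a change of analysis wording and slightly more programming, with no new data, visits or patients.
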